## Abstract

**Background:**

Intimate partner violence (IPV) is a pervasive public health problem, impacting the health and quality of life of survivors worldwide. The trauma of IPV is associated with a high incidence of mental illness, namely depressive and anxiety disorders, and posttraumatic stress disorder (PTSD). Moreover, literature endorses cognitive behavioral therapy (CBT) interventions as a gold standard for those with symptomatology consistent with anxiety disorders, mood disorders, and PTSD. However, efficacy has not been evaluated among a population of pregnant survivors of IPV.

**Objective:**

We present the protocol that will be used to explore the efficacy of trauma-informed cognitive behavioral therapy on maternal and child health outcomes for pregnant women with PTSD, depression, or anxiety symptomatology resulting from IPV. A secondary aim will be to test the validity and feasibility of study methodology to support the successful implementation of a full-scale randomized controlled trial.

**Methods:**

The Promoting Attachment Through Healing (PATH) study will use a mixed-methods approach grounded in an intersectional feminist framework to explore the effectiveness of trauma-informed CBT for pregnant survivors of IPV. Study participants will be recruited through the hospital-based Perinatal Mental Health Clinic (London, Ontario, Canada). A feasibility sample of 20 pregnant women (cohort 1) will be selected to engage in an eight-session antenatal CBT intervention facilitated by the program’s perinatal clinical nurse specialist, with evaluation at baseline, at two months postpartum (intervention and online questionnaire), and at six and twelve months postpartum (online questionnaire only). Concurrently, we will conduct a retrospective audit of 100 medical charts (cohort 2; 50 charts of perinatal women who received CBT and 50 charts of women who did not receive perinatal CBT) from the past five years. The efficacy of the intervention will be based on a reduction of mental illness symptomatology, improved maternal-infant attachment, maternal coping, and maternal quality of life. Additionally, the feasibility of the protocol and acceptability of the intervention from the women’s perspective will be examined. Inductive content analysis of all qualitative data will be used to determine common themes. Additionally, descriptive statistics, including measures of central tendency and dispersion, will be computed for all continuous variables. Alternatively, frequency tables will be constructed for all categorical variables.

**Results:**

The work reported here is in the proposal phase. Once the protocol is implemented, we will report the results in a follow-up paper. Participant recruitment for cohort 1 has started and we have finished data collection for cohort 2. It is anticipated that the results will be available by the end of 2018.

**Conclusions:**

Findings will assess the acceptability of the study methodology and protocol for a full-scale randomized controlled trial. Furthermore, if CBT is proven effective for pregnant survivors of IPV, this intervention could be readily adopted by health care and social support services, thereby contributing to an improved standard of care for this unique population.

**Trial Registration:**

ClinicalTrials.gov NCT03536442; https://www.clinicaltrials.gov/ct2/show/NCT03536442 (Archived by WebCite at http://www.webcitation.org/6zeurv1ay)

**Registered Report Identifier:**

RR1-10.2196/9820

## Introduction

### Background

Intimate partner violence (IPV)—a term that encompasses any act of physical, sexual, or emotional abuse within the context of coercive control by an intimate partner [1]—is a significant public health concern [2]. Intimate partner violence does not discriminate based on socioeconomic status, culture, or religion, and research indicates the global burden disproportionately impacts women [3], with gender-based violence deeply rooted in the patriarchal values espoused throughout history [4]. According to the most recent Statistics Canada profile on family violence, nearly 92,000 cases of IPV were reported to police in 2015, and of those, 79% of survivors were women [5]. While these numbers are deeply unsettling, it is perhaps more alarming that an estimated 1 in 4 Canadian women will be affected by IPV in their lifetime [6].

Ultimately, chronic victimization and coercive control [1] can have truly devastating consequences, including significant mental health challenges that follow survivors across the lifespan [7-9]. A recent meta-analysis and systematic review of 41 studies found women who had experienced IPV were considerably more likely to be diagnosed with a depressive disorder, anxiety disorder, or posttraumatic stress disorder (PTSD) [10]. Importantly, such disorders are more prevalent during pregnancy [10-12], with many studies suggesting the perinatal period poses an elevated risk of IPV [13,14].

Pregnancy is a time of significant physiological change [9]. Newly acquired fatigue, physical pain and discomfort, and emotional irregularity greatly impact one’s ability to cope with environmental stressors and engage in health promotion behaviors [15-17]. When combined with the intimate and invasive nature of perinatal care, it is not surprising that this time period may be traumatic and potentially triggering (in relation to PTSD) for survivors of IPV [18,19]. This is especially salient for those with symptomatology of depression, anxiety or PTSD [7,11,20]. Additionally, the highly-medicalized nature of prenatal interventions, labor and delivery, and postpartum care further contributes to feelings of vulnerability and powerlessness, thereby compromising the mental health and wellbeing of at-risk women [21]. Collectively, these factors substantially increase the likelihood of obstetrical complications including infant prematurity, low birth weight, and developmental delays [22-24]. Furthermore, such trauma and poor mental health are known to negatively impact maternal-child attachment [25], which can significantly affect the development of the child over the course of their lifespan [26-28].

Despite the pervasive nature of IPV and its deleterious health and social sequelae, particularly affecting childbearing women, there remains a considerable dearth of nursing and allied health literature evaluating mental health interventions for this population [29]. There is a critical need for individualized, trauma-informed care to facilitate optimal maternal and child health outcomes across the lifespan [29,30]. Fortunately, viable treatment options, such as cognitive behavioral therapy (CBT) exist to address such challenges; however, research exploring the efficacy of CBT among pregnant populations is lacking. As such, the purpose of the aptly named Promoting Attachment Through Healing (PATH) study is to test the suitability of CBT for the treatment of IPV-related depression, anxiety, and/or PTSD among pregnant women, which can in turn foster meaningful maternal-infant attachment and improve overall health and well-being.

### Objectives

The two overarching goals for this pilot study are: (a) to explore the efficacy of trauma-informed cognitive behavioral therapy (henceforth referred to as CBT) on maternal and child health and attachment outcomes for pregnant women with PTSD, depression, or anxiety symptomatology, resulting from IPV; and (b) to test the feasibility and acceptability of study methodology to support the successful implementation of a full-scale randomized controlled trial. To assess the ability of the proposed research to achieve the desired effect, we present five objectives:

To determine the impact of antenatal CBT on PTSD symptomatology among at-risk childbearing womenTo determine the impact of antenatal CBT on depressive symptomatology among at-risk childbearing womenTo determine the impact of antenatal CBT on anxiety symptomatology among at-risk childbearing womenTo determine the impact of antenatal CBT on maternal-infant attachment among at-risk childbearing womenTo determine the feasibility of the study protocol, by evaluating its process coherence, resource requirements, and perceived value through participant feedback

## Methods

### Design

This pilot project will consist of two cohorts: participants receiving CBT (cohort 1), as well as a retrospective chart audit of individuals who participated in the same CBT treatment within the last five years (cohort 2, intervention arm), and participants who received the accepted standard of care (cohort 2, standard care).

#### Cohort 1

A sample of 20 women currently attending the hospital-based, outpatient Perinatal Mental Health Clinic (London, Ontario, Canada) will be invited to participate in an eight-session antenatal CBT program facilitated by the clinic’s perinatal clinical nurse specialist (PCNS). CBT is currently the gold-standard approach for treating depression and anxiety. What is unique about this intervention is that it is tailored to the antenatal period and integrates attachment theory. Typically, women undergo initial screening at their pre-admission appointment for signs and symptoms of depression, anxiety, and PTSD, as well as for history of IPV. If women meet any of these criteria, they are referred for in-hospital social work or psychiatry consultations as necessary. While this intervention is currently provided to a small subset of women receiving antenatal care at the clinic, its efficacy remains untested. As such, this is considered a “specialty service” provided to identified at-risk women, and is not considered the accepted standard of care at this time.

#### Cohort 2

A retrospective medical chart review of 100 women will be conducted. All women must have received antenatal care at the recruiting hospital within the last five years and screened positive for IPV. This time frame was selected as it is representative of the duration in which the clinic’s current PCNS has been providing CBT to at-risk women. Of the 100 charts selected, 50 women must have participated in the CBT program (intervention arm), while the remaining 50 who did not will be assigned to the standard care group (these participants would have been eligible to participate but were not referred due to either lack of knowledge of the CBT program or a lack of support of the CBT program by the main health care provider). A sample size of 50 for both groups (intervention arm and standard care) will be sufficient to determine the feasibility of the study protocol for a future large-scale randomized control trial (RCT) [31].

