### Recruitment

#### Cohort 1

Participant recruitment will be facilitated through the PCNS at the London Health Sciences Center (LHSC) in the Perinatal Mental Health Clinic. Women who are receiving antenatal care at the clinic and meet the above eligibility requirements will be provided with a business card, should they wish to learn more about the study. To mitigate any undue influence or pressure to partake in the pilot project, potential study participants will be informed that their involvement is voluntary, and their involvement with the study will have no impact on the nature or quality of care. Participants interested in the study will be asked to contact the research team, at which time the safety protocol will be enacted, and eligibility and recruitment will be completed.

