A data abstraction instrument (developed by the co-principal investigators) will be used to collect data. Data will be pulled from multiple sources including: the e-chart, nursing chart, paper chart, and nursing care plan. Maternal data extraction will include: a) scope of mental illness, including diagnosis and current treatments; b) general physical and mental health status; c) obstetrical history; d) birth summary; e) care plan, including CBT interventions; f) evidence of learned CBT strategies or alternative coping strategies used during birth; g) birth experience; h) evidence of maternal-infant attachment; and i) demographics. Conversely, data extraction for infants at the time of parturition will include: a) gestational age; b) weight; c) length; d) head circumference; e) complications and interventions; f) Appearance, Pulse, Grimace, Activity, and Respiration (Apgar) score; and g) newborn physical exam. The chart review will take place at the recruiting hospital and does not require any patient contact. No identifying information will be collected, as the audit will be conducted for each chart in its entirety during a single data extraction period, thereby eliminating the need to refer back to any particular patient’s chart.

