#### Feasibility

Feasibility of the intervention and protocol will be evaluated through the semistructured interviews with women in cohort 1. To ascertain feasibility, open-ended questions will be asked to evaluate fidelity and resource requirements. Fidelity will be assessed by examining the five core components of the intervention with global open-ended questions for each, such as:

What have you learned about the brain (and the brain during pregnancy)?What have you learned about the nature of trauma and its effect on the brain?What have you learned about the effects trauma can have on your attachment with your baby?What have you learned about triggers?What tools have you learned about to manage triggers?

Resource requirements will be assessed from: 1) a provider perspective by tracking the length of the CBT sessions and the number of sessions; 2) a patient perspective by tracking any costs incurred to participate in the CBT session (eg, travel, childcare, etc); and 3) a system perspective by tracking the use of facilities and referrals to other resources.

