### Power

#### Cohort 1

A sample of 20 women was selected as this is a feasibility study and it is anticipated we will reach saturation (assessed by the sole interviewer with the use of field notes) in the qualitative data [46]. This sample will be used to inform future power analysis for the large-scale RCT.

#### Cohort 2

One hundred charts will be audited (50 from each of the two arms, the intervention and standard care arms). This sample size, for this feasibility study, was selected as it will allow us to extend the breadth and depth of analysis from cohort 1. This ultimately enhances the validity of the study’s findings [31] by contextualizing the differences between the intervention and standard care, therefore contributing to valuable knowledge translation.

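### Fifty charts per group cannot determine the feasibility of a future RCT at any sample size; feasibility has to be judged from cohort 1 counts, with the interviews in support

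*Protocol article*

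**What the plan says.** All references are to the Protocol article.

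- **Design, Cohort 2** makes the claim: 50 charts in each group "will be sufficient to determine the feasibility of the study protocol for a future large-scale randomized control trial (RCT"). It supports this with a citation. The same paragraph fixes the sample by treatment: 50 women who took part in the CBT program and 50 who did not.
- **Power, Cohort 2** gives another reason for the same charts. The number "was selected as it will allow us to extend the breadth and depth of analysis from cohort 1", and the audit is meant to put the difference between CBT and standard care in context.
- **Objectives** defines the feasibility objective: it is to be met "by evaluating its process coherence, resource requirements, and perceived value through participant feedback".
- **Outcome Measures, Feasibility** names the source: "Feasibility of the intervention and protocol will be evaluated through the semistructured interviews with women in cohort 1". The section adds tracking of the number and length of CBT sessions, participant costs, use of facilities, and referrals.
- **Data Collection, Cohort 2**: "The chart review will take place at the recruiting hospital and does not require any patient contact".
- **Recruitment, Cohort 1**: eligible women "will be provided with a business card, should they wish to learn more about the study", and those interested then contact the research team.
- **Data Collection, Cohort 1**: interviews take place at T1 (before CBT) and T2 (two months postpartum). T3 and T4 are questionnaires only.

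**The concern.** The second overarching goal of the study is to support a full-scale RCT. What such a trial most needs from a pilot is how many eligible women come forward, how many consent, whether they would accept random allocation, how much of the treatment they receive, and how many remain to the last assessment. The Design section credits the chart audit with settling feasibility, but the audit observes women who were never approached for a study, never asked to consent and never followed up under a protocol.

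Two things are at stake. A reader of the results could take 100 completed chart audits as evidence that the RCT is feasible. And if the weight falls instead on the interviews, the answers given after CBT come only from women who enrolled and were still in the study at T2, who may be more favourable than those who did not call or were lost.

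**Working it through.** **1. Can the figure of 50 per group be reproduced?** No. The article gives no significance level, power, effect size, standard deviation, expected rate or precision target for cohort 2. The Power section states only the size ("One hundred charts will be audited (50 from each of the two arms, the intervention and standard care arms")) and a narrative reason. There is no formula to run, so no arithmetic error can be shown either.

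**2. What would the chart numbers buy as precision?** For a proportion p, the Wald 95% half-width is 1.96 × √(p(1−p)/n). At p = 0.5, where it is widest:

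- n = 50: 1.96 × √(0.25/50) = 0.139, or ±13.9 points
- n = 100: 1.96 × √(0.25/100) = 0.098, or ±9.8 points

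This is precision for variables recorded in charts. It does not carry over to quantities the charts do not hold.

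**3. Which feasibility quantities can the audit observe?**

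| Quantity for the RCT | Cohort 2 charts | Cohort 1 |
|---|---|---|
| Uptake among women approached | No: the CBT share is 50/100 = 50% by design, and non-recipients were not referred because of provider knowledge or support | Yes, if cards and contacts are counted |
| Consent to a study | No: no patient contact | Yes |
| Acceptance of randomisation | No | Not observed; could only be asked about |
| Sessions received under the protocol | Indirectly at most: CBT entries in past care plans | Yes: number and length of sessions are tracked |
| Retention at T2, T3, T4 | No: no study follow-up | Yes: from returns at each time |
| Participant feedback (the Objectives' own definition) | No | Yes |

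Charts with less than half of the required data are excluded under the Inclusion Criteria, so even completeness of routine data would be estimated from a truncated sample.

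**4. Who answers the post-CBT questions?** The fidelity questions ask what the woman has learned, and three of the four acceptability questions ask what CBT has changed or whether she would recommend it. T1 precedes CBT, so on the stated schedule T2 is the only interview at which they can be answered. By status:

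- never called after receiving a card: no interview
- enrolled, lost before T2: T1 only, nothing after CBT
- stopped CBT but stayed in the study: T1 and T2 both possible
- lost after T2: both interviews already given

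**5. What precision can cohort 1 counts give?** Exact (Clopper-Pearson) 95% limits for x of n are the 0.025 quantile of Beta(x, n−x+1) and the 0.975 quantile of Beta(x+1, n−x). The article gives no rates, so these are assumed:

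- 16 of 20 (80%): 0.563 to 0.943
- 14 of 20 (70%): 0.457 to 0.881
- 10 of 20 (50%): 0.272 to 0.728

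For uptake, if approaches are logged until 20 women enrol:

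- assumed 30%: 20/0.30 ≈ 67 approached, interval 19% to 42%
- assumed 50%: 20/0.50 = 40 approached, interval 34% to 66%
- assumed 70%: 20/0.70 ≈ 29 approached, interval 49% to 85%

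**The case against.** The strongest reply is that this is one loosely worded sentence in a condensed article. It rests on a citation that cannot be seen here, and the rest of the article places feasibility in cohort 1. Much of that is fair, and several stronger readings should be resisted:

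- **That 50 is a miscalculated number.** Nothing supports this. No inputs are given and the cited source is not available. The fault is a mismatch between data source and purpose.
- **That the charts are uninformative.** They abstract care plans including CBT, evidence of learned strategies, and birth and infant outcomes. They can also show whether 50 CBT recipients existed in five years. That is useful context.
- **That the interviews miss everyone who drops out.** T2 is set by time since birth and is not conditional on finishing CBT. The session, cost and referral tracking is not confined to retained women.
- **That no retention figure will exist.** It can be read from the returns at T1 to T4.
- **That the plan lacks recruitment logs, progression thresholds or any question on randomisation.** An article commonly leaves these to the full protocol. The fidelity questions are given as examples, and the interview guide is not shown.

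Some acceptability questions also look ahead to labor and an unborn child, which may point to an antenatal occasion that the article does not list; the reasoning about T2 rests on the schedule as stated.

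What the reply does not remove is that the sentence gives the audit a property it lacks at any size, and that it disagrees with three other sections. The citation cannot repair that, because the conflict lies within the article.

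**Conclusion.** The point stands as a conflict between the Design section on one side and the Objectives, Feasibility and Power sections on the other, and as a claim the audit cannot deliver. The shortfall is one of kind: for consent, acceptance of randomisation and study retention, 100 charts supply no observations, and uptake is fixed at 50% by the sampling.

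The selection in the interviews is real but limited. It affects the post-CBT feasibility and acceptability answers, and it concerns women who never enrol or are lost before T2. How many that will be is unknown, since the article gives no expected uptake or loss.

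Cohort 1 can supply uptake, session and retention figures, imprecisely. The intervals shown rest on assumed rates and illustrate what 20 women can yield; they do not measure an error in the plan. The Limitations section already concedes that the sample is small. The matter is worth correcting because the second goal depends on it and the correction is nearly free.

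**What to change.** 1. In Design, Cohort 2, delete the sufficiency sentence, or reword it to agree with the Power section: cohort 2 provides context on CBT and usual care.
2. State that feasibility is judged in cohort 1 from counts of women given a card, making contact, eligible and consented; sessions attended of eight; and returns at T2, T3 and T4. Report each with its denominator and an exact 95% confidence interval.
3. Keep the interviews as supporting evidence on fidelity and acceptability, and report how many women gave a post-CBT interview out of those enrolled.

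**Cost.** A change of wording and a tally by existing staff, part of which the planned session tracking and questionnaire returns already supply. No extra participants are needed. There are two drawbacks. Intervals will be wide with 20 women. And because the abstract reports that cohort 1 recruitment has started, cards already handed out may not be recoverable; where they are not, the count should run from now on and the report should say so.
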